### 3.5. Training of the Pharmacists

Mandatory communication training will enhance treatment integrity since pharmacist skills and competences will determine the quality of the intervention. Before the study begins, CPs in the intervention arm will receive training involving both theoretical and practical sessions. It will cover the prevalence, risk factors, complications, and diagnosis of hypertension, as well as non-pharmacological ways of preventing it. On the practical side, CPs will learn how to measure blood pressure using a manual sphygmomanometer, interpret the measurements, and educate and counsel hypertensive patients through audio–visual presentations. As part of the intervention strategy, blood pressure control, the identification of hypertension-related complications, health education, medication and lifestyle modification counseling, follow-up, and referral to a medical practitioner or hospital will be provided.

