### 3.2. Study Participants

As part of the consensus, participants who come to the pharmacy to purchase hypertensive medication will be listed with their basic information. The following information will be needed: their name, address, gender, duration of hypertension, who will be taking the medication, and at least two contact numbers. In order to confirm whether prospective hypertensive adults are hypertensive, their blood pressure will be measured again. Both male and female participants will be invited to participate. The eligibility criteria include (1) aged 18 years and above; (2) hypertensive (defined as (a) SBP ≥ 140 mmHg and DBP ≥ 90 mmHg and/or taking antihypertensive medications); (3) capable of communicating verbally in local language; (4) permanent resident of the study area; (5) access to mobile phone; and (6) consent to participate. Exclusion criteria are (1) pregnant and lactating women; (2) individuals with advanced medical disease (e.g., cancer, heart failure, chronic obstructive pulmonary disease, end-stage renal disease, advanced neurological disease, etc.); (3) those having cognitive and psychiatric problems; (4) involvement in any other interventional study; and (5) individuals who are unable to give informed consent. Pharmacists’ inclusion criteria include (1) ensuring a sufficient amount of time to implement intervention on hypertensive patients; (2) consent to participate; and (3) being able to operate a smartphone or tablet. Screening for patients’ eligibility will be conducted by the CP during regular visits, and upon deeming them eligible, the CP will inform the principal investigator or research assistant of this study to approach the patients, briefly explain the study, and ask them to sign informed consent.

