### 3.4. Blinding

Only the outcome evaluators will be blinded to group allocation due to the nature of the intervention. To prevent contamination, we will select the CPs of the treated group and control from considerably different locations. CP will deliver the intervention, and research assistants (field enumerators and supervisors) will engage in data collection from the participants. However, pharmacists and research assistants will not be blinded since they are involved in interventional processes.

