** *Assessment and intervention* **												
Selection criteria	x	x	x	x								
Informed consent	x	x	x	x								
Randomization					x							
Allocation					x							

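### The order of allocation, pharmacist training and patient screening is left ambiguous, and the baseline blood pressure behind the primary outcome is scheduled after allocation

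*Protocol article*

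**What the plan says.** All references are to the protocol article.

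- **Training (Section 3.5).** "Before the study begins, CPs in the intervention arm will receive training involving both theoretical and practical sessions". The content includes diagnosing hypertension and measuring and interpreting blood pressure.
- **Screening (Section 3.2).** "Screening for patients’ eligibility will be conducted by the CP during regular visits". The pharmacist then alerts the research team, who explain the study and take consent. Blood pressure is checked again to confirm hypertension, but this reading is not said to be the analysis baseline.
- **Order of events (Table 2, Section 3.3).** Table 2 marks selection and consent in weeks 1 to 4 and randomization and allocation in week 5. Month 0, labelled baseline, comes next. Section 3.3, which follows the section on participants, also describes randomization as the next step.
- **Blood pressure (Table 2, Section 3.7).** Table 2 schedules it at months 0, 6 and 12 in both arms. Section 3.7 lists it among the data that enumerators collect, in connection with a risk score.
- **Blinding (Section 3.4).** "Only the outcome evaluators will be blinded to group allocation due to the nature of the intervention". The section adds that "research assistants (field enumerators and supervisors) will engage in data collection from the participants" and that "pharmacists and research assistants will not be blinded since they are involved in interventional processes".
- **Primary outcome (Section 3.8).** Change in systolic and diastolic pressure between baseline and month 12.

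**The concern.** In a cluster trial, randomizing pharmacies makes the pharmacies comparable. It makes the patients comparable only if they are identified without regard to the arm. If a pharmacist knows the pharmacy is in the intervention arm and has already been trained, the patients referred may differ from those a control pharmacist refers, for example in motivation or severity. Later adjustment removes only the part of that difference that was measured.

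The baseline reading raises a separate issue. The primary outcome subtracts it from the month 12 reading. If it is taken by staff who know the arm, any arm-related tendency in measurement enters the outcome directly. Neither problem shrinks as the sample grows.

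**Working it through.** The plan gives no figure on this point. The Bangladesh sample size (40 pharmacies x 90 patients = 3,600) is the same whichever order applies. The check is a comparison of the stated sequences, then a short piece of algebra on how each kind of error reaches the primary outcome.

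**Step 1: what Section 3.5 requires.** Training only the intervention pharmacists requires that allocation is already known. The open question is when the study begins.

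| Meaning of study start | Implied order | Fit with Table 2 |
|---|---|---|
| Week 1, start of screening | allocate, train, screen and consent, baseline | Conflicts: Table 2 allocates in week 5 |
| Month 0, baseline survey | screen and consent (weeks 1-4), allocate (week 5), train, baseline | Agrees |

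Section 3.6 lends some support to the second row, because it counts the project's phases from the baseline survey. Section 3.14 leans the other way with its loose wording that equal numbers are to be recruited for each group. No sentence settles it.

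**Step 2: consequence of the first row.** Pharmacists do the screening, are not blinded, and in one arm only would already have training that bears on eligibility. The article describes no safeguard, such as a recruiter unaware of the arm or a participant list closed before allocation.

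**Step 3: consequence under both rows.** In each, the first scheduled blood pressure (month 0) falls after allocation. Section 3.7 assigns collection to enumerators. Section 3.4 counts field enumerators among the research assistants who are not blinded. Section 3.6 also puts the baseline survey and the first session in one phase.

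**Step 4: how errors reach the primary outcome.** Let Y0 and Y12 be mean pressure at baseline and month 12 in the intervention (I) and control (C) arms. The contrast is

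D = (Y12_I - Y0_I) - (Y12_C - Y0_C).

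- *Measurement error at baseline.* If arm-aware measurement adds e mmHg to Y0_I alone, D becomes D - e. The error passes in full into the difference in change, and a positive e looks like a larger reduction.
- *Difference in who is recruited.* If intervention patients have a true level d mmHg higher at both times, the contrast contains +d - d = 0. A pure difference in level cancels. Recruitment biases D only if the patients would also have changed differently, through regression to the mean or a different trajectory.

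The document gives no value for e, for d, or for differences in trajectory, so no size follows.

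**The case against.** The strongest reply is that there is no contradiction. Table 2 is the explicit timetable, and it puts recruitment before allocation, which is the protection one would ask for. Speaking of pharmacists in the intervention arm presupposes that allocation has happened, and training between week 5 and month 0 fits every section. Figure 1, which is not available here, may make the order clearer. Much of this stands: a reader might infer that Section 3.5 flatly contradicts Table 2, but the documents support only an ambiguity with one harmless reading and one harmful one.

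This reply does not reach the baseline measurement, which Table 2 itself places after allocation. There the defence is that outcome evaluators are blinded. Section 3.4 does not say that they are a separate group who take blood pressure, and the staff it describes as collecting participant data are the unblinded ones. The screening check in Section 3.2 precedes allocation under Table 2, but is not named as the baseline.

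A reader might also want a number. Assuming a systolic SD of 20 mmHg and a shift of 0.10 to 0.25 SD gives 0.10 x 20 = 2 to 0.25 x 20 = 5 mmHg, or 40% to 100% of the 5 mmHg that Section 3.8 calls clinically relevant. The documents do not support this. Neither input appears in them, and Step 4 shows that a recruitment difference in level does not carry one-for-one into a change score.

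**Conclusion.** The point holds in two parts of different strength.

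1. **Training and screening.** The text is ambiguous. Read literally, Section 3.5 has arm-aware, already trained pharmacists selecting patients. It fits Table 2 only on the unstated assumption that the study begins at month 0.
2. **Baseline after allocation.** This holds on either reading. The first scheduled blood pressure follows allocation and is assigned to staff described as unblinded, and the primary outcome is change from it. It rests on taking the enumerators' reading in Section 3.7 as the month 0 measurement in Table 2. The article names no other collector for that row.

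The size of any bias is unknown and cannot be derived from the document. The conclusion is that the plan leaves an avoidable route to bias open, not that a bias of a given size will occur.

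**What to change.** - **Section 3.5:** state that intervention pharmacists are trained after the week 5 allocation and before their first patient session.
- **Table 2:** move baseline blood pressure and the baseline questionnaire into the week 1 to 4 screening and consent contact, ahead of the randomization row.
- **Sections 3.2 and 3.3:** state that each pharmacy's participant list is closed once baseline is complete, and that allocation is generated and revealed only then.

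With this order nobody can know the arm at baseline, so the enumerators' blinding status no longer matters for that reading. Who measures at months 6 and 12, and whether they know the arm, is a separate matter that Section 3.4 should also make clear.

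**Cost.** Sample size and intervention content do not change, and patients are already seen for consent and a blood pressure check in weeks 1 to 4. The change does separate the baseline survey from the first session, which Section 3.6 joins. It needs some rescheduling of fieldwork across 44 pharmacies (40 + 4) and about 3,960 patients (3,600 + 360). It also leaves a gap of up to a few weeks: a patient measured in week 1 waits about four weeks for allocation (5 - 1), plus training time. The gap should be kept the same in both arms.

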### 3.6. Intervention

This project will consist of three phases: baseline survey with first-time intervention implementation; second intervention at 6 months; and third, endline survey at 12 months. The details of the intervention content are mentioned in Table 1. As part of the intervention within the randomized selected groups, the CP will conduct two 15–30 min sessions throughout the intervention period, once at the baseline or first visit (T0) and once at the sixth month (T1). Patients will attend the two sessions at the pharmacies where they collect their prescription medication. Face-to-face counseling sessions will be held about hypertension and its management, including lifestyle changes and drug compliance. Patients will be able to view the educational material in the pharmacy via a tablet since audio–visual presentations make learning easier. The detailed training material and handbook are presented as Supplemental Files S1 and S2. To maintain adherence to intervention, the intervention group will receive phone call intervention at 3 months and 6 months. The patient will be reminded every time about their subsequent visits via phone calls/short message services (SMS). Patients’ BP will be monitored routinely during each session, and information regarding medication and complications will also be obtained. This intervention will be low in cost, aligned with the current CP workflow, and will not require any significant changes in the existing system. Both interventions will be conducted by the same pharmacist to ensure consistency. Furthermore, CPs in the intervention group will receive a checklist of items and a counseling protocol to prepare them for what they need to do during patient visits. A pilot study was conducted in two pharmacies in Bangladesh before starting the study in order to optimize the intervention steps and materials. Nevertheless, there are no restrictions on how many times the patient may meet the pharmacists outside of these ‘core’ consultations. In this case, the patient will decide with the pharmacist according to needs, and it is suggested that this coincides with the monthly collection of prescriptions.

In the control group, routine pharmacy services and counseling will be provided without interference during all pharmacy visits, as per each country’s pharmacy practice guidelines, and they will serve as a comparator group to determine the impact of the intervention implementation. Assessments will be completed at the same time points as those in the intervention group.

### 3.7. Data Collection

Data will be collected primarily through a face-to-face interview with an open-ended structured questionnaire. The interview team will comprise graduates in social science, public health, demography, and statistics with extensive experience in survey techniques, along with two experienced supervisors who will oversee the survey. They will all undergo four days of mandatory training and two days of practical sessions focused on the questionnaire content, techniques to obtain more information from study subjects, and strategies for acquiring complete and valid data. An operational manual will be provided to both interviewers and supervisors to ensure clarity on the research purpose. The supervisor will be responsible for regularly monitoring the intervention process. The details about the data collection time point are mentioned in Table 2.

At baseline, after obtaining informed consent by the interviewer, data will be collected on the self-reported basic socioeconomic and demographic characteristics of the patients, such as age at the completion of the questionnaire, gender, highest level of education completed, occupation, religion, and marital status. Also, the basic characteristics of the CP (age, gender, and working experience in the community pharmacy in years) will be collected. Information on disease profiles will be obtained by face-to-face direct interview and used to inform the consultation at each stage. The following data will be requested from patients and CP at baseline and 12 months via questionnaire or pre-defined data collection form (as appropriate):Clinical factors of the patients [time since diagnosis of hypertension in years; types of concomitant antihypertensive medications; development of any hypertension-related complications such as coronary heart disease (CHD), and heart failure and stroke; in the previous six months: (i) occurrence of any adverse health condition related to hypertension requiring hospitalization; (ii) total number of days in hospital following admission; and (iii) total number of visits to doctors for hypertension and its related complication management;Organizational information of the community pharmacies (number of visits from hypertensive patients per month in last six months, number of hypertensive cases referred to hospital due to complications in last six months);Quality of life measure (EuroQol EQ-5D-5L) [28].

Additional data will be collected by enumerators to enable the calculation of the QRisk2 score, including the following:Blood pressure (lowest of two measurements used);Fasting blood glucose level;Weight and height;Smoking status (options aligned with QRisk2).

For the economic evaluation, all costs related to pharmacy-based intervention will be collected including patient counseling and education time and training, telephone and material costs, cost of care at the hospital (for complicated cases requiring visits to physicians and admission), and other administrative costs.

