### 3.8. Outcome Evaluation

The primary effectiveness of the outcome will be evaluated by changes in the SBP and DBP of the patients from baseline to final follow-up at 12 months post-intervention. The secondary outcome measures will include (1) BP controlled to target (SBP < 140 mmHg and DBP < 90 mmHg); (2) composite outcome of death (all-cause) or hospital admission due to CHD, heart failure, or stroke; (3) incremental cost per HRQoL gained from baseline to end of follow-up; (4) improvement in the knowledge of patients on healthy lifestyle; (5) change in dietary salt intake; (6) change in quality of life; (7) change in the prevalence of current smokers; and (8) the treatment adherence rate. Hypertensive patients with poor adherence to their treatment regimens experience uncontrolled blood pressure. Adherence to hypertension treatment is defined as following the treatment regimen agreed to with their physician. According to the previous literature [29,30,31], a reduction of 5 mmHg of SBP is considered clinically relevant as it has been found to be significantly associated with a risk reduction in CHD, stroke, and other serious cardiovascular events. Health service utilization parameters will include the number and reason for visits to physicians and hospital admission, and when further complicated, the death of the patient. The cost-effectiveness measures are incremental cost per mmHg BP reduction or cost per HRQoL gained from baseline to end of follow-up at 12 months. For determining dietary salt intake level, a 24 h urinary sodium measurement will be opted.

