## 5. Limitations

The main limitation could be the high dropout rate as patients may be too busy to attend an educational session, some might lose interest and discontinue during the study period, and some participants might miss their routine follow-up visits due to political unrest or any other unavoidable circumstance. Although the patients’ presence can never be guaranteed, the research team and the CP will try their best to contact and persuade patients to participate. Secondly, missing data can be an issue in this trial; however, the planned analyses will follow intent-to-treat methods to minimize bias from dropout over time. A repeated-measurement bias can also be expected as the same questionnaire will be used at both baseline and endline surveys. Finally, due to the short follow-up duration, the long-term benefits of this CP model may not be observed at length. Despite these limitations, the study findings can give a basis for improving the future care of hypertensive patients in primary healthcare facilities in South Asia.

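### The composite counts all-cause death, but the stated sources and analysis set do not separate a death from a dropout, and intervention-only contacts may make events better known in that arm

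*Protocol article*

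**What the plan says.** All references are to the protocol article.

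- **Outcome.** Section 3.8 lists as a secondary outcome the "composite outcome of death (all-cause) or hospital admission due to CHD, heart failure, or stroke". It also names the patient's death among the health service utilization parameters. Table 2 places the composite at months 6 and 12 for both groups.
- **Source.** Section 3.7 states: "Data will be collected primarily through a face-to-face interview with an open-ended structured questionnaire". It continues: "The following data will be requested from patients and CP at baseline and 12 months via questionnaire or pre-defined data collection form". The patient items are complications and, for the previous six months, admission for a hypertension-related condition, days in hospital and doctor visits. There is no item for vital status or date of death.
- **Analysis set.** Section 3.10 says that patients who complete all scheduled follow-ups are analysed. It also calls for strict intention to treat, as does Section 3.13.
- **Attrition.** Section 5: "The main limitation could be the high dropout rate".
- **Contacts in the intervention arm only.** Section 3.6 says that at pharmacist sessions "information regarding medication and complications will also be obtained", and that "the intervention group will receive phone call intervention at 3 months and 6 months". Table 2 also restricts the calls to this arm but marks months 3 and 9. Section 3.5 trains intervention pharmacists to identify complications and adds that "referral to a medical practitioner or hospital will be provided".
- **Control arm.** Section 3.6 gives routine pharmacy services, with assessments at the same time points.
- **Tracing data already held.** Section 3.2 collects "at least two contact numbers" for each listed patient.

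**The concern.** A patient who has died cannot be interviewed and cannot complete follow-up. Nothing in the stated sources, items or analysis set separates that patient from someone who stopped attending. This applies in both arms and threatens the death component as a whole.

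The second issue is balance. The pharmacist is a named informant in both arms, but what the pharmacist is likely to know differs. In the intervention arm the informant is trained on complications, holds a scheduled session after baseline, and is part of a programme that phones patients. In the control arm the informant sees whoever happens to come in. If more true events become known in the intervention arm, that arm looks worse than it is.

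Reduced hospitalization and death is one of the stated hypotheses (Section 2.1). The introduction presents the effect on mortality and admissions as new evidence, and both enter the cost-effectiveness ratios in Section 3.13. A distorted count would carry through to all of these.

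**Working it through.** **1. What happens to a death under each analysis rule**

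- Completers (Section 3.10): every patient who dies before month 12 is left out, in both arms. The composite reduces to admissions among survivors who completed. This loses the death component but does not by itself favour an arm.
- Intention to treat (Sections 3.10 and 3.13): the patient stays in, but counts as an event only if someone reports the death. With no vital-status item and no informant other than the pharmacist, this depends on what the pharmacist knows.

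**2. What happens to an admission**

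Section 3.7 asks at baseline and month 12 about the previous six months. Read alone, it misses admissions in months 0 to 6 after enrolment, in both arms. Table 2 adds a month-6 assessment of the composite, which would close the gap. The two places do not agree.

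**3. Which contacts differ by arm after baseline**

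| Contact | Intervention | Control |
|---|---|---|
| Assessments at months 6 and 12 | yes | yes |
| Pharmacist as data source (Section 3.7) | yes | yes |
| Routine pharmacy visits | yes | yes |
| Month-6 session asking about complications | yes | no |
| Phone calls and visit reminders | yes | no |
| Training to identify and refer complications | yes | no |

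The month-6 session falls at the same time as an assessment held in both arms. The added contact is therefore mainly the calls, the reminders and any optional visits, together with the training.

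**4. Size, as an illustration only**

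The document gives no event rate, expected event count or capture rate for the composite. Its only sample-size figure is for blood pressure: 2 × (1.960 + 0.842)² × 49.78² / 4.65² gives 1800 per arm, or 3600 in total, as stated for Bangladesh. Only the 1800 per arm is used below.

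Recorded risk = true risk × share of events captured. With equal true risk, the recorded risk ratio is the ratio of the capture shares, whatever the true risk.

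Assumed: true risk 2% in both arms; capture 95% (intervention) and 80% (control).

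- True events: 1800 × 0.02 = 36 per arm.
- Recorded: 36 × 0.95 = 34.2 against 36 × 0.80 = 28.8.
- Recorded risk ratio: 0.95 / 0.80 = 1.19 with no true effect.
- A true risk ratio of 0.80 would appear as 0.80 × 0.95 / 0.80 = 0.95.

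Over a range of control capture, with the intervention arm held at 95%:

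| Control capture | Null appears as | True 0.80 appears as |
|---|---|---|
| 95% | 1.00 | 0.80 |
| 90% | 1.06 | 0.84 |
| 80% | 1.19 | 0.95 |
| 70% | 1.36 | 1.09 |

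If only deaths are captured unequally, the distortion is diluted. Suppose 12 of the 36 events are deaths (95% against 80%) and 24 are admissions (95% in both arms). The control arm then records 12 × 0.80 + 24 × 0.95 = 32.4, and the ratio is 34.2 / 32.4 = 1.06.

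The false-positive rate of a two-sided 5% test at 2% risk and 95% against 80% capture, with design effect 1 + 89 × ICC for 90 patients per pharmacy, is 10.5% at ICC 0, 7.9% at ICC 0.01 and 6.0% at ICC 0.05. The ICCs are also assumed. At these event counts the main harm is a shifted estimate rather than a false significant result.

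**The case against.** The other side has a good deal in its favour.

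- The pharmacist is a source in both arms, and Section 3.7 sets no arm restriction. A reader might infer that the control arm has no route by which an event becomes known. The document does not support that.
- The session text concerns medication and complications, not deaths, and the calls are there to support adherence. A reader might infer that deaths are sought at sessions or by phone. No passage says so, and none says that this information enters the outcome data. That such contacts reveal events is a reasonable inference, but only an inference.
- Deaths are meant to be counted: Section 3.8 names them, Table 2 schedules the composite in both groups, and Section 3.13 uses mortality.
- This is a condensed article, and Section 3.7 mentions an operational manual that is not shown. A tracing procedure may be there, so its absence alone would be no finding.
- Referral belongs to the intervention, and one might want to set aside the admissions it prompts. That would condition on something that happens after randomization and because of it. It would remove more events from the intervention arm and could create a bias in its favour. An admission for one of the three named causes counts whoever referred the patient.

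What remains is that the items and the completer rule that are printed do not fit an outcome containing death. The intention-to-treat statements conflict with the completer rule and do not supply a source. Equal assessment dates do not equalize what the informants know.

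**Conclusion.** The point holds as a risk, not as a demonstrated bias. As written, deaths can merge with dropout in either arm, and the completer sentence would remove them from both. Unequal contact and training make it possible that events are learned of more often in the intervention arm, which would probably work against the intervention.

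A reader might go further and conclude that control deaths will be recorded as dropout and that the comparison is biased. The document supports neither as fact, and the size cannot be derived from it. The ratio of 1.19 rests wholly on the assumed capture of 95% against 80%. It falls to 1.06 if only deaths, taken as a third of events, are captured unequally, and to 1.00 if capture is equal.

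The outcome is secondary, so the primary blood pressure comparison does not depend on this. The change should still be in place before follow-up, because a death classed as dropout is hard to recover later.

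**What to change.** 1. At months 6 and 12, in both arms, have the enumerators complete one common form for every randomized patient: vital status, date of death, and admissions with cause since the last assessment.
2. For every patient not interviewed, have the enumerator call the contact numbers collected at listing and ask a relative. The article does not say whose numbers these are, so confirm at baseline that one reaches a household member.
3. Build the composite only from this form, for all randomized patients including those who died. Report patients whose status stays unknown separately, by arm. Keep pharmacist session and call records as process data.
4. Reconcile Section 3.7 with Table 2 on when events are collected, and the completer sentence in Section 3.10 with the intention-to-treat statements there and in Section 3.13. The call months in Section 3.6 and Table 2 also need to be reconciled.
5. A field for whether an admission followed a pharmacist referral may be added for description only. It should not define an analysis that excludes events.

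The cost is one form and some extra call time for enumerators already in the field. Research assistants are unblinded (Section 3.4), so the calls should follow a fixed script with the same number of attempts in both arms.
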